## Abstract

**Background:**

Borderline personality disorder (BPD) is a common mental disorder that severely impairs patients’ psychosocial functioning and quality of life and results in prolonged use of health services. Although psychotherapy is recommended as the most effective treatment for patients with BPD, their complex emotional needs can be met in everyday clinical practice by developing integrative, holistic, personalized mental health services tailored to their needs.

**Aim and hypothesis:**

The aim of our study was to evaluate the effectiveness of a specialized psychodynamic stepped-care service for BPD patients. Our hypothesis is that patients receiving this specialized health-care service will show greater improvement in clinical, functional and quality of life than patients receiving a treatment as usual (TAU) service. In addition, specialized health-care services will prove to be more cost effective.

**Method and design:**

A quasi-experimental clinical trial will be conducted. The study is designed to include 212 BPD patients who will be non-randomly assigned to specialized health care services and to two TAU centers. Patients will be recruited at each site following the routine clinical pathways of referral at each center. The primary outcome measures are BPD severity, suicide attempts and hospital admissions. The secondary outcome measures will include measures of general psychopathology, psychosocial functioning, quality of life and retention in treatment. In addition. An economic evaluation from a societal perspective will be conducted.

**Discussion:**

The development of complex individualized stepped-whole care public interventions for BPD patients requires extended research in everyday clinical practice conditions. In this study, we describe the design and implementation of a pragmatic trial to evaluate this type of health service for BPD patients, and we discuss the strengths as well as the problems and how these can be mitigated.

**Trial registration:**

Clinical Trials gov.: ClinicalTrials.gov ID: NCT06392139 (Protocol ID No. 404/06-07-202).

## Background

Borderline personality disorder (BPD) is a common mental disorder characterized by pervasive and persistent instability in interpersonal relationships, identity and affect, and marked impulsivity (1). BPD patients present high rates of comorbid mood, anxiety, substance use, eating, and other personality disorders (2, 3). BPD patients’ quality of life (QOL) is severely impaired across mental and physical dimensions (4, 5), and their social functioning is consistently poor (6). In addition, BPD patients often experience significant emotional crises, engage in self-harm injury, and make suicide threats or attempts (7, 8), resulting in extensive use of treatment services (emergency departments or inpatient hospitals) (9–12). People with BPD commit suicide at a rate of 10% (13). The point prevalence of BPD is estimated to be 1% in community settings (14).

Reports range from 0.7% to 2.7% for lifetime prevalence (15); however, a previous study in a nonclinical sample (16) reported a higher lifetime prevalence of 5.9%. In clinical settings, BPD is one of the most common PDs, with a point prevalence of approximately 12% in outpatients and 22% in inpatient psychiatric populations (14). Furthermore, 6.4% of patients in primary care settings have a BPD diagnosis (10). Epidemiological studies tend to define BPD as a categorical entity. However, compelling evidence suggests that we should understand BPD as a dimensional construct rather than a categorical one (14, 17). Even low levels of BPD symptoms, not only full-blown BPD, are associated with psychiatric comorbidities and functional disability (17).

Previous research has highlighted the increased economic burden of BPD on society due to the extensive use of health services, loss of productivity (11, 18, 19), and intersectoral costs (20). The economic burden of personality disorders, including BPD, appears to be greater than that of depression and generalized anxiety disorder and comparable to that of schizophrenia (11).

Researchers recommend psychotherapy as the first-line treatment for BPD (21, 22). Despite the poor evidence for pharmacotherapy efficacy, clinicians often use psychotropic medications to treat specific symptoms and comorbid psychiatric disorders or when psychotherapy is not accessible (13, 23, 24). Researchers have developed several psychotherapy approaches for the treatment of BPD over the last three decades. It has been shown that cognitive behavioral models (such as schema therapy and dialectical behavior therapy) and psychodynamic therapies (such as transference-focused psychotherapy and mentalization-based therapy) work well and do not cost too much to treat BDP symptoms (e.g., 21, 25, 26).

The increased, complex needs of BPD patients and the need for individualized care for BPD (25), led to the development of different treatment modalities and different integrated programs. These include intensive residential programs (e.g., 28–32), step-down programs (e.g., 33–35), day hospital programs (e.g., 28, 36, 37), and community-based psychotherapeutic models (e.g., 38, 39). These programs are multimodal, may include group and/or individual (mostly psychodynamically oriented) psychotherapy, art and/or drama therapy, psychosocial activities (26, 27) in combination with psychiatric management and symptom-targeted pharmacotherapy (28, 29). Besides, several studies point out the effectiveness of moderate intensity programs compared to more intensive and residential programs ones (26, 27, 30).

In addition, integrated intervention models have been developed that combine cognitive-analytic psychotherapy with general psychiatric care, with a focus on prevention and early intervention for BPD youth (31–33).

However, recent studies still point to a lack of integrative and personalized focus in the treatment of BPD (22, 34, 35). Mental health services for people with personality disorders are still considered to be “doubly disadvantaged”, as they appear to lag significantly behind services for people with other long-term mental health conditions (25). The current literature suggests that people with BPD should receive care that is effective and affordable, that adheres to the general principles of good care for people with personality disorders (36), and that provides rapid post crisis follow-up and prolonged treatment (7, 37). Specifically, there are robust recommendations for integrative whole-service approaches that provide a personalized stepped care model with a combination of psychological and psychiatric treatment interventions, ensuring that patients receive tailored care (7, 22, 25, 38). The involvement of families and relatives in care and therapy is also recommended (34). Although BPD is primarily defined behaviorally and diagnostically, neurobiological research has uncovered consistent disruptions in frontolimbic circuits (39, 40), neurochemical imbalances including serotonergic, dopaminergic, and oxytocinergic dysfunctions (41, 42), and epigenetic mechanisms such as altered gene expression in stress-response systems (43, 44). These findings support integrative models that combine neurodevelopmental vulnerability with environmental stressors to explain emotional dysregulation and interpersonal instability in BPD (45). Despite extensive research into the effectiveness of specific psychotherapies for patients with BPD, there is a lack of pragmatic studies evaluating the effectiveness of stepped health care services that provide treatment for BPD as a whole-care approach (25). Individuals with BPD face both severe psychological symptoms and systemic stigma or neglect. Specialized, integrated treatment programs remain insufficient, particularly within under-resourced public mental health systems. This study advocates for increased investment in long-term, tailored care to address these gaps and promote equitable access to treatment.

Furthermore, in a time of economic crisis, in a budget-constrained health care system, it is crucial to gather information on the costs and benefits of a public sector service to inform decisions on resource investment (46, 47). However, few studies have evaluated the effectiveness and cost-effectiveness of specialized stepped health care services in the public health care system for patients with BPD compared with treatment as usual (TAU). In the 1^st^ Department of Psychiatry of the Medical School of the National and Kapodistrian University of Athens, a psychodynamic specialized stepped health care service named the “Specialized Therapy Program for BPD patients” (STP-BPD) was developed in 1999 (28, 29, 48). Researchers have previously positively evaluated the clinical effectiveness of an earlier inpatient model, which is based on the same psychoanalytic concepts as the STP-BPD (29), but they have not yet investigated the effectiveness and cost-effectiveness of the whole stepped care service in comparison to TAU.

The current service is based on a multimodal treatment approach, offering a variety of specific treatment options, including psychoanalytically oriented group psychotherapy, pharmacotherapy, and monthly follow-up consultations by psychiatrists. All of these treatment services are structured and delivered within a stepped care model, which is consisted of two phases: an initial preparatory one aiming to welcome the patient and provide a facilitating environment to prepare him for the second phase of the specific psychotherapeutic interventions. A second phase where patients are assigned to long term psychoanalytically oriented psychotherapies (mainly group psychoanalytic psychotherapy as well as individual psychoanalytic psychotherapy, group or individual art therapy or a day hospital program. Alongside psychotherapy, patients receive psychiatric management and pharmacotherapy if required. Given the current need for more conclusive verification of the clinical effectiveness and cost-effectiveness of specialized stepped health care services for BPD patients, further research is needed to provide robust evidence on their capacity to produce the aforementioned critical outcomes optimally.

In light of the above, the current article describes and discusses our longitudinal study protocol, which pertains to the research purposes, the implementation context of a specialized stepped care model for BPD patients, our rationale for selecting a naturalistic-pragmatic design, both the primary and secondary outcomes, and the instruments employed for their assessment over a 2-year follow-up. Finally, we discuss the importance of our study aims and the insights they provide.

## Aims and hypotheses

The primary aim of this study was to evaluate whether our specialized stepped care service for BPD patients, namely, the STP-BPD would produce better outcomes for treated patients than would the standard TAU service over a longitudinal 2-year follow-up evaluation at four different time points after participant enrollment. The primary outcomes of this study address the severity of BPD manifestations as well as the symptoms of self-harm and suicidality. Furthermore, we conduct an evaluation of the costs of health care services, as well as an evaluation from a societal perspective. A crucial challenge for BPD-specific health care services would be to improve the general psychopathology; the interpersonal, psychosocial and occupational functions; and the quality of life of patients. These domains are addressed by our study’s secondary outcomes.

Additionally, we will examine the mediating effects of reflective functioning and various aspects related to personality organization, such as defense mechanisms. More specifically, we hypothesize that improvements in reflective functioning during the initial phase of treatment will predict reductions in BPD symptoms and self-injurious behavior at later stages. Age will be treated as a moderator variable in line with evidence regarding the course of the disorder, the symptoms of which, tend to decline with age (49).

In addition to the abovementioned main objectives, this study aims to translate, adapt, and analyze the psychometric properties of the instruments employed in the present research among the Greek population, as some of them have not yet been rigorously evaluated. This investigation is currently in progress for most instruments, apart from those whose Greek versions have already shown satisfactory psychometric properties. Our hypotheses are as follows: 1) Participants receiving specialized stepped care services will exhibit greater clinical improvement, and specialized stepped care services will prove to be more cost-effective than TAU services. 2) Compared with participants receiving standard TAU, those receiving specialized service will exhibit greater functional improvement as well as enhanced QOL. 3) The differences discerned in the outcome variables between the two groups are expected to be mediated by differences in reflective functioning, defense style and personality organization.

Moreover, a longer-term evaluation will take place for both groups but only for the primary outcome variables, as the interview entailing both primary and secondary outcomes is long and by extending the evaluation time frame, we would not want to lose participants at longer follow-ups and risk the emergence of attrition bias.

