We designed this study to evaluate the effectiveness and economic aspects (cost-effectiveness and cost-utility) of the STP-BPD in everyday clinical practice, adhering to the call for *‘real-world’* clinical trials (55, 56). Therefore, we will use minimal exclusion criteria without altering clinical decision-making, health care, or treatment. Patients will be followed for 2 years for primary and secondary outcomes, and for additional 3 years for primary outcomes only. Assessment of the clinical and psychosocial outcome variables will be performed at baseline (T_0_), prior to patient allocation, and every 6 months until the end of the 2^nd^ year of follow-up (T_1_, T_2_, T_3_, and τ_4_). At baseline (T0) and then every year thereafter (τ2 and τ4), the mediators that affect the link between the type of health care service and the major clinical and psychosocial outcomes will be examined. For long-term evaluation, primary outcome variables will also be assessed at T_5_ (2 years and 6 months), T_6_ (3 years), T_7_ (3 years and 6 months), T_8_ (4 years), T_9_ (4 years and 6 months) and T_10_ (5 years). Patient flow, screening and assessments are displayed schematically in **Figure 1**.

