### Treatments

#### The STP-BPD

In the STP-BPD at Eginition Hospital, people with borderline personality disorder can receive psychoanalytic psychotherapy (59), along with other psychiatric services such as psychiatric evaluation, counseling, medication therapy, and hospitalization if needed (28, 29). In addition to existing treatments, additional therapies (i.e., arts-based therapies) are offered (22). The program bases its integrative approach and clinical practice on Bion’s (60) container/contained model, aiming to establish a broad framework known as the *‘Psychodynamic setting’*. The stable and secure *‘psychodynamic setting’* acts as a receptive container, absorbing the intense projections and projective identifications of the BDP patients, their frequent acting-outs, and the countertransference reactions of the clinicians, and enabling thinking over time, helps the patient internalize the containment capacity (28, 29), which lowers acting-out episodes and improves clinical symptoms.

Central to this approach is its team-based nature, which provides a supportive environment for mental health professionals (61), reduces splitting among them, and enhances their containing function. To this end, weekly staff meetings are held.

As mentioned above, the Program has a stepped care approach with two different steps/phases of intervention:

1. *The reception outpatient clinic* is the initial phase of the intervention, through which BPD patients enter the program. First, psychiatric and psychological eligibility assessments are carried out. Then, for a period of 6–8 months, the reception outpatient clinic offers eligible patients psychoanalytically oriented therapy sessions (1 session per month), psychiatric management sessions, and, if indicated, pharmacotherapy (1 session per month). The first phase of the program, which adheres to a stepped care approach, aims to provide a *‘holding’* environment for patients, manage their ambivalence about therapy, and prepare them for the next phase, which offers intensive psychotherapy. The initial phase also allows for the mental health care of a large number of patients before the more intense interventions of the second phase are available. The capacity of the reception outpatient clinic is 50 patients. Crisis management for patients during phase 1 included visits to the Emergency Department of the Eginition Hospital.

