### Mediators

**Reflective Functioning Questionnaire (RFQ**) (88, 89): This is a brief, screening measure of reflective functioning. It has been developed to assess severe impairments or imbalances in mentalizing, which are typically observed in patients with borderline personality disorder features. Through confirmatory factor analyses, the two factors—certainty (RFQ_C) and uncertainty (RFQ_U)—were found to be fairly different. They remained the same across clinical and nonclinical samples and had good internal consistency and test-retest stability. The RFQ has satisfactory reliability and test–retest reliability. The estimates of internal consistency for RFQ_U and RFQ_C were.77 and.65, respectively, in the clinical sample and.63 and.67, respectively, in the nonclinical sample. The test–retest reliability over a period of 3 weeks was excellent, with *r*
_s_ = .84 and.75 for RFQ_U and RFQ_C, respectively, all *p* =0.001 (88).

**Defense Style Questionnaire (DSQ-40)** (90): The 40-item version of the DSQ-40, derived from the original measure developed by Bond, Gardner, Christian, and Siegel (91), is a widely used self-report measure for defense mechanisms because of its easy administration and cost effectiveness. It aims to assess behavior indicative of conscious derivatives of defensive styles that correspond to hypothesized patterns of unconscious psychological mechanisms (90).

The **Inventory of Personality Organization (IPO)** (92, 93) is a self-report instrument intended to measure a patient’s level of personality organization. We constructed the scale to cover five personality dimensions, with the first three serving as the primary clinical scales. These scales assess the degree of identity pathology, the level of immature defensive mechanisms (Primitive Defenses, PD), and the degree of impairment in the ability to test reality (Reality Testing, RT). The three IPO scales demonstrate adequate internal consistency and good test–retest reliability. Lenzenweger (92) reported that the three main dimensions of an IPO’s first psychometric properties in adult and psychiatric samples are internally consistent: identity diffusion (α = .84–.90), reality testing (α = .85–.87), and primitive defenses (α = .80–.87). Confirmatory factor analysis at the item level supported a two-factor structure of the IPO, which is consistent with Kernberg’s model of borderline personality organization (92).

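### The early-change hypothesis for reflective functioning has no measurement that isolates the initial phase: the RFQ is first repeated at 12 months, after a phase stated to last 6–8 months

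*Protocol article*

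**What the plan says.** All places are in the protocol article.

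- **Hypothesis (Aims and hypotheses).** One mechanism is given a time order: "improvements in reflective functioning during the initial phase of treatment will predict reductions in BPD symptoms and self-injurious behavior at later stages". Numbered hypothesis 3 is more general. It expects group differences to be mediated by reflective functioning, defense style and personality organization, and sets no timing.
- **Meaning of the initial phase (Background; The STP-BPD).** Background describes two phases, the first being "an initial preparatory one aiming to welcome the patient and provide a facilitating environment to prepare him for the second phase". The treatment section says of the reception outpatient clinic that it "is the initial phase of the intervention, through which BPD patients enter the program", and that "for a period of 6–8 months, the reception outpatient clinic offers eligible patients psychoanalytically oriented therapy sessions".
- **RFQ schedule (Design; Table 1).** "At baseline (T0) and then every year thereafter (τ2 and τ4), the mediators that affect the link" between service type and outcome are to be examined. Table 1 agrees: RFQ at T0, T2 and T4. It shows a T1 visit at 6 months with nine other instruments but no RFQ.
- **Analysis (Mediation analysis).** Group assignment is the independent variable and reflective functioning the mediator in Model 1, with analyses at T2, T4, T6, T8 and T10. No early-change score or lag is stated.
- **Outcome recall (Primary outcome measures).** The BPDSI looks back three months and the Suicide and Self-Harm Inventory six.

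**The concern.** The hypothesis is about when reflective functioning changes. Testing it needs a value at or near the end of the initial phase and outcomes recorded afterwards. The schedule gives no RFQ value between baseline and month 12. The first change score, T0–T2, therefore combines the preparatory phase with part of the more intensive second phase, and no later analysis plan can recover a value that was not collected.

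At T2 the time order is also weak. The first RFQ change and the outcome come from the same visit, and the outcome instruments describe the months before it.

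This matters because the article leans on the mechanism. Under Limitations and challenges it argues that specifying the pathway of change supports internal validity in a design without random allocation. If T0–T2 change were read as early change, that argument would rest on a measure that cannot tell preparation from the second-phase therapies.

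**Working it through.** The plan gives no figure of its own on this point. The sample size does not enter, so the check is one of timing.

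**Inputs**
- Length of the initial phase, L: 6 to 8 months (The STP-BPD).
- RFQ visits: months 0, 12 and 24 (Design; Table 1).
- General visits in the first two years: months 0, 6, 12, 18 and 24 (Design).
- BPDSI and Suicide and Self-Harm Inventory visits: T0 to T10 (Table 1).
- Recall: BPDSI 3 months, self-harm inventory 6 months (Primary outcome measures).

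**Step 1. RFQ values within the initial phase.** Post-baseline RFQ months are 12 and 24. Neither is 8 or less, so the count is zero. A general visit at month 6 does fall within the phase.

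**Step 2. How much of T0–T2 lies in phase 2.** Let w be any delay, either before phase 1 begins or while waiting for a phase 2 place. Months in phase 2 before T2 = 12 − L − w, not below zero.

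| w (months) | L = 6 | L = 8 |
|---|---|---|
| 0 | 6 (50%) | 4 (33%) |
| 2 (assumed) | 4 (33%) | 2 (17%) |
| 4 (assumed) | 2 (17%) | 0 (0%) |

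Only the row w = 0 follows from the stated durations. The other rows are illustrations, because the article gives no waiting times. It does say that phase 2 entry depends on clinical criteria and availability, with therapy groups opening twice a year and the day hospital once, and that T0 precedes allocation. The mixture will therefore differ between patients.

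**Step 3. Time order at T2.** T2 outcomes cover months 12 − 3 = 9 to 12 (BPDSI) and 12 − 6 = 6 to 12 (self-harm). The RFQ is completed at month 12, so both outcome periods lie before it. No other post-baseline RFQ value exists for this analysis to use.

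**Step 4. What later visits allow.** At T3 (month 18) the outcomes cover months 15–18 and 12–18, so a T0–T2 RFQ change precedes them. The two instruments are scheduled at eight visits after T2 (T3–T10). If the RFQ were given at T1, nine would follow (T2–T10), and the T2 windows (months 9–12 and 6–12) would start at or after the month 6 RFQ.

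**Step 5. How well T1 marks the end of the phase.** At month 6, 6/8 = 75% to 6/6 = 100% of the stated phase has passed, assuming it starts at T0. T1 thus falls 0 to 2 months before the scheduled end, and more for patients who wait.

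**The case against.** The strongest reply is that the hypothesis sentence names no number of months. The 6–8 months come from the description of the specialized service, TAU has no phases, and the sentence belongs to a mediation aim that compares both groups. Against group therapy lasting 3 years and primary-outcome follow-up of 5 years, the first year could be called early, and T0–T2 change would then serve. This reading is possible, but the article never adopts it. It uses the word initial for the first phase in Background and in the treatment section. If the first year was meant, the wording needs to change. The lack of phases in TAU stands as a reason to define the period in calendar time.

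A reader might infer that the mechanism cannot be tested at all, or that few later outcomes remain. The documents do not support that. The two outcome instruments run to T10, and the mediation analyses at T6, T8 and T10 must use an RFQ value from T4 or earlier, which puts the mediator first. What is lost is isolation of the initial phase, not every test of earlier change against later outcome. By visit count, adding T1 gains one visit: nine against eight.

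It is also fair that waiting lowers the share of T0–T2 spent in phase 2, so 33–50% is what the stated schedule implies and not a figure for every patient. Finally, nothing in the article says that a T0–T2 association will be presented as early change. That is a risk, not a stated plan.

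**Conclusion.** The mismatch is real and internal to the article. Under its own use of the term, the initial phase lasts 6–8 months in the specialized service, and no RFQ is scheduled between baseline and month 12. Change in that phase cannot be separated from change in the first part of phase 2: about 4–6 of the 12 months if phase 1 starts at T0 and ends on schedule, and less for patients who wait. The T2 mediation analysis does not have the time order that the hypothesis claims.

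The reach is limited. RFQ change to T2 can still be related to outcomes at T3–T10, numbered hypothesis 3 can still be examined, and the primary group comparison is not touched. The conclusion rests on reading the hypothesis by the article's own phase definition. On the looser first-year reading the repair is one of wording and of dropping T2 as a test of prediction.

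**What to change.** This is a cheap improvement.

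1. Add the RFQ at T1 in both groups, in the Design section and in Table 1. The article itself says of it: "This is a brief, screening measure of reflective functioning".
2. State the test as RFQ change from T0 to T1 against BPDSI and self-harm from T2 onward, adjusted for the T0 and T1 values of the outcome. This also gives TAU a calendar definition of the early period.
3. If the form is not added, or for patients already past T1, reword the hypothesis as change during the first 12 months. Relate T0–T2 RFQ change only to outcomes from T3 onward, and do not use T2 as a test of this hypothesis.

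Cost: a short amendment and a few minutes of patient time at an existing visit. T1 values will be missing for patients already past that visit; the article does not say how many there are. Those patients would come under the 12-month wording, so the two analyses should be reported separately. T1 may also fall up to two months before phase 1 ends on the stated durations, and earlier relative to its end for patients who wait, so it approximates the end of the phase.
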